**Methods/Design:**

The study will include PMO patients (postmenopausal women; aged between 50 and 70 years; have been postmenopausal for at least 5 years and diagnosed with OP using proximal femur T-score) with concomitant lumbar OA (patients with confounding disorders like diabetes, hypertension, hyperlipidemia, and previous fracture history, *etcetera*, will be excluded) will be randomly assigned to two arms: PEMFs group and sham PEMFs group. There will be 25 participants in each arm (50 in total) and the outcome assessment, including the primary endpoint (proximal femur bone mineral density), will be performed at 5 weeks, 3 months and 6 months after enrollment.

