### Sample size

Because we could not identify data or citations proving references for the minimum clinically significant difference and corresponding standard deviation in proximal femur bone mineral density (BMDF) between the two arms, the “least detectable longitudinal change measured using dual-energy X-ray absorptiometry (DXA), that is, 0.023” was approximately used as the expected absolute intergroup difference and standard deviation [20, 27]. With a type I error probability of 5 % and a 90 % probability of avoiding a type II error, we would require 20 participants in each group. Assuming a loss to follow-up of 20 %, a total sample size of 50 participants (25 participants per group) is needed.

We did additional sample size calculation for pain intensity, the most important secondary endpoint, measured using the Visual Analogue Scale (VAS) on a scale of 0 to 100. With a standard deviation of 32.17 [28], type I error of 5 %, 90 % power, and a 20 % drop-out rate, approximately 25 patients would be needed in each group to show a minimum clinically significant difference, 30-points between groups [29].

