#### Health economics evaluation

To determine whether the PEMFs are cost-effective to pay for additional health gain, we will compute mean (and SD) per patient costs and incremental cost-utility ratios using quality-adjusted life-years (QALYs) derived from SF-36 scores with appropriate preference weightings [35, 36].

For all the analyses mentioned above, a two-sided value of *P* <0.05 will be considered statistically significant. All statistical analyses will be carried out using 19.0 SPSS software (SPSS, Chicago, IL).

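### The VAS pain calculation's 25 per group does not give 90% power after 20% drop-out under the two-sided 5% level the protocol sets for all analyses

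*Protocol article*

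**What the plan says.** The Sample size section of the protocol article contains two calculations. The first, for proximal femur bone mineral density, arrives at 20 per group, allows for 20% loss to follow-up and concludes that "a total sample size of 50 participants (25 participants per group) is needed".

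The second is for pain: "We did additional sample size calculation for pain intensity, the most important secondary endpoint, measured using the Visual Analogue Scale (VAS"), on a 0 to 100 scale. Its inputs are given as "With a standard deviation of 32.17 [28"] and "type I error of 5 %, 90 % power, and a 20 % drop-out rate". Its result is that "approximately 25 patients would be needed in each group to show a minimum clinically significant difference, 30-points between groups". Drop-out is listed among the inputs, so the 25 reads as a number to enrol. It also equals the planned arm size in the abstract: "There will be 25 participants in each arm (50 in total").

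The Sample size section does not say whether the 5% is one-sided or two-sided. The end of the Data analysis section, under Health economics evaluation, does: "For all the analyses mentioned above, a two-sided value of" P below 0.05 is the criterion for significance.

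**The concern.** Under the two-sided level, 25 per group is roughly the number of evaluable patients that the VAS inputs require, before any allowance for loss. If a fifth are lost, as the protocol assumes, 20 per group remain, and 20 do not give 90% power for 30 points.

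The stake is how a VAS result would be read. The Background makes the simultaneous effect on osteoporosis and osteoarthritis the primary goal, and VAS is the only outcome on the osteoarthritis side with a power statement. A non-significant VAS result would be set against a stated type II error of 10%, when a simple comparison of 20 completers per arm carries about 16% to 18%.

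**Working it through.** **Inputs.** Difference 30 points, SD 32.17, type I error 5%, power 90% and drop-out 20% (Sample size). Two-sided testing (end of Data analysis). Two equal arms of 25 (abstract, Sample size). Standardised difference: 30 / 32.17 = 0.9325.

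**1. Evaluable number, two-sided 5%.** The normal approximation is n = 2 × (z₁₋α/₂ + z₁₋β)² × (SD/difference)².

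- (1.960 + 1.282)² = 10.51; (32.17/30)² = 1.150
- n = 2 × 10.51 × 1.150 = 24.2, so 25 per group
- The t-test (noncentral t) gives 25.2, so 26 per group

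Power at 25 evaluable per group is 90.9% (normal) or 89.8% (t). So 25 matches the stated 90% only if nobody is lost.

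**2. Allowing for 20% loss (divide by 0.8).**

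| Basis | Evaluable per group | Enrolled per group |
|---|---|---|
| Normal, unrounded | 24.16 | 30.2, so 31 |
| Normal, rounded up first | 25 | 31.25, so 32 |
| t-test, rounded up first | 26 | 32.5, so 33 |

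The stated 25 is 6 to 8 per group below these.

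**3. Can the stated 25 be reproduced with drop-out included?** With a one-sided 5% level and the normal approximation:

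- (1.645 + 1.282)² = 8.56; n = 2 × 8.56 × 1.150 = 19.7, so 20 per group
- 20 / 0.8 = 25 enrolled

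That is the stated figure exactly (the one-sided t-test gives 21, then 27). Two-sided 5% at 80% power gives 19, then 24, and at 85% power 21, then 27, but both contradict the stated 90%.

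There are therefore two routes to 25: two-sided without inflation, or one-sided with it. The bone density calculation does not settle which was used. With a difference equal to the SD, the normal formula gives 22 per group two-sided and 18 one-sided, and the stated figure is 20.

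**4. Power of the planned size, two-sided.** 25 × 0.8 = 20 evaluable per group.

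- Normal: 0.9325 × √(20/2) − 1.960 = 2.949 − 1.960 = 0.989, which gives 83.9%
- t-test: 82.0%

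**5. Difference detectable with 90% power at 20 per group.**

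- t-test: 33.8 points
- Normal: 32.17 × 3.242 × √(2/20) = 33.0 points

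**The case against.** Four arguments deserve weight.

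- **Cause.** A reader might infer that the drop-out step was simply forgotten. The document does not support that. Sidedness is not stated in the Sample size section, and a one-sided calculation reproduces 25 with drop-out applied. The bone density calculation just before it does inflate from 20 to 25. This objection stands as far as the cause goes. It does not rescue the figure, because no one-sided test is planned anywhere.
- **Power of the actual analysis.** A reader might also infer that the trial as planned has 82% power for VAS. That goes too far. The 82% describes an unadjusted comparison of 20 completers per arm. The plan carries the last observation forward for anyone with at least one post-randomization value, so the number analysed may exceed 20, though carrying values forward can also dilute or bias the effect. The mixed model adjusts for the baseline value. If 32.17 is the SD of raw scores (an assumption, since its source is not at hand), dividing the standardised difference by √(1 − r²) gives t-test power at 20 per group of about 85%, 88% and 91% for a baseline correlation r of 0.3, 0.4 and 0.5. This objection stands too, but the sample size text relies on neither feature and gives no correlation, so its statement remains unsupported as written.
- **Importance.** VAS is secondary, the calculation is described as additional, and the total of 50 comes from the bone density endpoint. Power of 82% to 84% is still respectable for a secondary endpoint. This limits the severity.
- **Disclosure.** The Discussion concedes that the sample size calculation is imprecise and calls the trial preliminary. The risk it goes on to name is type I error, so the VAS power is not corrected there. The word used to hedge the 25 cannot cover a gap of 6 to 8 patients per group.

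**Conclusion.** The VAS statement is wrong as written. Under the two-sided 5% level the protocol sets for all analyses, its inputs need 25 to 26 evaluable and about 31 to 33 enrolled per group, against a stated 25. Either drop-out was left out or a one-sided level was used without being stated. The document does not show which, and neither gives 90% power for the planned two-sided test.

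With 25 enrolled and 20 evaluable per group, power for 30 points is about 82% (t-test) or 84% (normal approximation), and 90% power is reached at about 34 points by the t-test. These figures rest on SD 32.17, equal arms, a full 20% loss and an unadjusted comparison of completers. They are not the power of the planned adjusted model.

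The severity is moderate: a stated power for a secondary endpoint needs correcting. Neither the sample size nor the primary analysis is called into question by this point.

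**What to change.** Keep the total at 50. State that the VAS calculation is two-sided, and replace the present sentence with one such as:

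> With 25 enrolled and 20 evaluable per group, an unadjusted two-sided 5% comparison has about 82% power (84% by normal approximation) to detect a 30-point VAS difference (SD 32.17), or 90% power for about 34 points.

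The claim that 25 per group covers both 90% power and 20% drop-out should go. The cost is one sentence and a less favourable stated power. Recruitment, endpoints and analyses do not change.

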### Assessment

The primary outcome will be the mean percentage change in BMDF at 6-month follow-up. Proposed secondary outcomes were listed below: VAS; The mean percentage changes in bone mineral density of the lumbar spine (BMDL); serum 25-hydroxy-vitamin D (25(OH) D) concentrations; Oswestry Disability Index (ODI); manual muscle test (MMT) score; Berg Balance Scale (BBS) score; Timed Up and Go Test (TUG); hemorheological determinants; serum C-terminal telopeptide of type I collagen (sCTX I), serum bone alkalin phosphatase (sBALP), N-MID osteocalcin (N-MID); range of motion (ROM) of lumbar spine; overall functional ability using short form 36 item general health questionnaire (SF-36, Quality Metric, Inc., Lincoln, Rhode Island, USA); treatment compliance; health care consumption costs; possible adverse events (Additional file 1). Detailed information on some of the outcome measurements are described below:

As for BMD measurements, participants will be scanned in the standard manner by a technician using DXA (GE Lunar iDXA with encore 12.0 software, GE Healthcare Lunar, Madison, WI) following recommendations from the manufacturer. For proximal femur, BMD of the total hip will be recorded and analyzed, while for the lumbar spine the average BMD (aBMD) of the four vertebrae (L1-L4) will be extracted. All these data could be directly obtained using corresponding software without further calculations.

Manual muscle strength of the lumbar and the lower-extremity will be estimated by employing the MMT method with the traditional six-point ordinal Medical Research Council scale (0 to 5). Half-point scores will be used between all grades except that of 4 and 5, since it requires manual resistance that cannot be graded reliably [30]. All tests will be performed by a single examiner. Furthermore, before testing, the examiner and participants will all be required to rest for at least 5 min.

The BBS is a set that comprises 14 simple balance related tasks, ranging from standing up from a sitting position, to standing on one foot [31]. Another examiner will perform the tests for all the participants following the standard procedure. The examiner and participants will also be required to rest for at least 5 min before testing.

A TUG test will be conducted by recording the total time that a person takes to rise from a chair, walk 3 meters, turn around, walk back to the chair, and sit down [32]. It is intended to evaluate the functional mobility of the participants.

Adverse events will be recorded throughout the study period. Having once occurred, the intensity and possible relationship with the treatment will be examined and described in detail.

Baseline assessment will be carried out after eligibility and informed consent has been confirmed (Fig. 1). Apart from outcome measurements, information referring to participant’s age (in years), menopause age (in years), time since menopause (in years), body mass index (BMI; in kg/m^2^), comorbidities, duration of low back pain symptoms, medication use, information referring to physical activity (evaluated by the International Physical Activity Questionnaire (IPAQ) short version [33]), sunlight exposure (frequency and duration of time spent outside, sun-protective-factor use), employment status, occupation and dietary intake will all be collected.

### Follow-up

After the first 5 weeks after enrollment, all participants are scheduled to receive only usual care and the research will go into the follow-up phase with scheduled follow-up visits taking place at 5 weeks, 3 months and 6 months after enrollment (Additional file 1). The last two time points are designed to explore possible delayed effects of PEMFs.

### Data analysis

Continuous measurements will be expressed as means and standard deviations (SD) and categorical measurements will be summarized using numbers and percentages. For all variables, descriptive statistics will be calculated.

Our primary analysis of the data will be performed using the principle of intention-to-treat (ITT). All participants with a baseline value and at least one measurement after randomization will be included in the efficacy analyses using the last observation carried forward (LOCF) method. It will consider all participants, including those who are not fully compliant and those with missing outcome data.

In addition, we will conduct sensitivity analysis by conducting a per-protocol (PP) analysis for the primary outcome at 6 months. It will include participants whose compliance is good, which is defined as attendance of all the scheduled visits, and low contamination (no other treatment during the first 5 weeks after enrollment).

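### LOCF in the primary analysis assumes no BMD change after the last visit and can bias the 6-month difference in either direction; the efficacy set is a modified ITT set

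*Protocol article*

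**What the plan says.** All references are to the protocol article.

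- **Endpoint (Assessment):** "The primary outcome will be the mean percentage change in BMDF at 6-month follow-up".
- **Visits (abstract, Methods/Design):** outcome assessment, including BMDF, "will be performed at 5 weeks, 3 months and 6 months after enrollment". The Interventions section ends active or sham treatment at 5 weeks.
- **Purpose of the later visits (Follow-up):** "The last two time points are designed to explore possible delayed effects of PEMFs".
- **Population and missing data (Data analysis):** the primary analysis is described as intention-to-treat. The set is then defined: "All participants with a baseline value and at least one measurement after randomization will be included in the efficacy analyses". The same sentence fixes the method for gaps: these participants "will be included in the efficacy analyses using the last observation carried forward (LOCF) method". The next sentence reads "It will consider all participants, including those who are not fully compliant and those with missing outcome data".
- **Model (Primary analysis):** a mixed linear model over the three follow-up visits, with treatment as a fixed factor and time as a random factor. No treatment-by-time term is named.
- **Sensitivity analyses:** a per-protocol analysis limited to participants who attended every visit and had no other treatment in the first 5 weeks (Data analysis), and t-tests on change to the end of follow-up (Primary analysis).
- **Planned loss (Sample size):** "Assuming a loss to follow-up of 20" per cent.

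**The concern.** LOCF gives a valid 6-month value only if nothing changes after the last visit attended. Whether something changes between 5 weeks and 6 months is what the 3- and 6-month visits are meant to find out, so the analysis assumes the answer to a question the design leaves open.

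The method is also unnecessary. A mixed model fitted by likelihood uses every observed visit of a participant who leaves early, without filled-in values, under a missing-at-random assumption. LOCF replaces that with a more specific assumption and treats carried-forward values as measured.

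At stake is the estimate on the primary endpoint of a 50-participant trial, where a few carried-forward values per arm carry real weight. The efficacy set also leaves out anyone randomized who has no later value, although it is presented as ITT.

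**Working it through.** **Planned loss.** The article's inflation reproduces: 20 / (1 − 0.20) = 25 per arm. A 20% loss is 0.20 × 25 = 5 per arm, or 10 of 50. That is the largest number of 6-month values that planned loss could cause to be carried forward, reached if every lost participant has a 5-week or 3-month value. (The base figure of 20 per arm is not at issue here.)

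**Formula.** Let e5, e3 and e6 be the between-group effects at 5 weeks, 3 months and 6 months, and w5 and w3 the shares last seen at 5 weeks and 3 months, equal in both arms, with w5 + w3 = 0.20. A simple 6-month contrast with LOCF has expectation

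0.80 × e6 + w5 × e5 + w3 × e3.

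The article gives no time course, so the profiles below are assumptions. Linear build-up puts e5 at 5/26 = 0.19 and e3 at 0.50 of the 6-month effect.

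| Assumed profile (e5, e3, e6) | All lost after 5 weeks | Even split | All lost after 3 months |
|---|---|---|---|
| Linear build-up (0.19, 0.5, 1) | 0.838 | 0.869 | 0.900 |
| Delayed (0, 0.25, 1) | 0.800 | 0.825 | 0.850 |
| Plateau by 5 weeks (1, 1, 1) | 1.000 | 1.000 | 1.000 |
| Partly waning (1.5, 1.25, 1) | 1.100 | 1.075 | 1.050 |
| Early, gone by 6 months (1, 0.5, 0) | 0.20 | 0.15 | 0.10 |

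Two cells in full:
- Linear, even split: 0.80 + 0.10 × 0.19 + 0.10 × 0.50 = 0.869.
- Vanished effect, even split: 0.80 × 0 + 0.10 × 1 + 0.10 × 0.5 = 0.15 of the peak, where the true 6-month effect is nil.

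On the article's planning difference of 0.023, linear build-up gives 0.023 × 0.838 = 0.0193 to 0.023 × 0.869 = 0.0200. That figure is an absolute difference while the endpoint is a percentage change, so the proportions are the safer summary.

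**Simulation.** 25 per arm, 5,000 runs, true 6-month effect 1 SD (the article's planning ratio, 0.023/0.023), assumed between-visit correlation 0.7, dropout completely at random within each arm. With equal loss, each arm loses 20%: 5% never seen after baseline, 10% last seen at 5 weeks and 5% at 3 months.

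- Linear build-up, equal loss: LOCF 0.89 SD, power 83%; observed 6-month values 1.00 SD, power 86%. Formula check: (0.80 + 0.10 × 0.19 + 0.05 × 0.50) / 0.95 = 0.89.
- Linear build-up, loss of 10% control and 30% active: LOCF 0.83 SD, power 78%, against 86% on observed values.
- No effect, equal loss: no material bias; LOCF rejects in 5.3–5.7% of runs, observed values in 5.3–5.5%.
- No effect, loss of 10% and 30%, common decline of 0.5–1 SD: LOCF shows a spurious 0.06–0.11 SD in favour of the active arm and rejects in 6.1–6.4% of runs.

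In the equal-loss runs, about 0.05 × 50 = 2.5 randomized participants have no post-baseline value and fall outside the efficacy set.

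**The case against.** **Conditional bias.** A reader might infer that LOCF necessarily biases the result because the protocol expects delayed effects. The Follow-up section only says that they are possible and will be explored, and no time course is given. There is no bias if the effect has plateaued by the last visit, or under no effect with equal loss. Unequal dropout does harm only where values or effects change over time. This stands, and the conclusion is worded accordingly.

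**Modest size.** The simulated power loss with equal dropout is about 3 percentage points, and the rejection rate under no effect stays close to 5%. For an effect that builds up late, the error is toward zero. The mixed model's own advantage rests on missing-at-random, which is also an assumption. This too stands.

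**The formula is not the stated model.** It describes a simple 6-month contrast. Read literally, the Primary analysis section has no treatment-by-time term and would give an effect pooled over visits. Under linear build-up that is (0.19 + 0.5 + 1) / 3 = 0.56 of the 6-month effect even with complete data. So LOCF is not the only source of dilution, and removing it alone would not isolate 6 months.

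**ITT contradiction.** A reader might infer that the Data analysis section contradicts itself. The sentence about considering all participants can be read as describing the set just defined: non-compliers and those missing a later visit stay in. What remains is a label.

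**An existing check.** The per-protocol analysis requires attendance at every visit, so it normally carries nothing forward. But it is a selective set of completers, also filtered on other treatment. The t-tests change the model, and the text does not say whether carried-forward values feed them. Neither replaces a sound primary analysis.

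None of this defends LOCF as the chosen method. The article fixes it explicitly, so it is not a detail left to an analysis plan.

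**Conclusion.** The point holds as a conditional one. LOCF on the 6-month endpoint assumes stability after the last visit, which the design treats as an open question, and with 20% loss up to one fifth of the values could rest on that assumption. For a simple 6-month contrast, it recovers about 84–87% of a linearly building effect (90% if all loss follows 3 months) and shows 15–20% of the peak of a vanished early effect (10% if all loss follows 3 months). It is unbiased under a plateau by 5 weeks. These figures rest on assumed time courses, equal loss in both arms and every lost participant having a post-baseline value.

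The documents do not support saying that the bias is certain, that its direction is known, or that type I error is seriously inflated. The efficacy set is a mislabelled modified ITT set, not a clear contradiction.

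**What to change.** 1. Delete LOCF from the primary analysis. It may stay as a supportive table.
2. Fit the planned mixed model by likelihood to all observed post-baseline BMDF values, analysed as randomized, with visit as a fixed factor and a treatment-by-visit term. Name the 6-month treatment contrast as primary.
3. Call the efficacy set modified ITT. With percentage change as outcome and baseline as covariate, the mixed model still draws nothing from participants without a later value, so step 2 does not make this a full ITT analysis.
4. Add a multiple-imputation sensitivity analysis that includes randomized participants with only a baseline value.

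The cost is a change of analysis wording, one extra analysis and a slightly wider interval. No participants or visits are added, and the article reports that the trial is still recruiting.

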### Interventions

All included participants will receive conventional usual care (600 mg/day calcium and alfacalcidol vitamin D supplement 0.25 μg/bid) throughout the study period. Participants allocated to the PEMFs group will receive additional PEMFs treatment (40 min/treatment, 1 treatment session/day, 6 treatment sessions/week, for a total of 30 times as one course of treatment) for the first 5 weeks after enrollment, while those assigned to the sham PEMFs group will receive sham PEMFs treatment with the same device but no stimulus generated, indistinguishable from the real ones.

The PEMFs treatment will be applied using XT-2000B therapeutic stimulators (Tianjin xtmed, Tianjin, China) to generate time-varying fields consisting of bursts of asymmetric pulses. Each burst should last for 0.2 ms and repeat at a frequency of 8 Hz. The fields will be delivered perpendicular to the lumbar spine and proximal femur of the supine participant and the flux density within a single burst will start with a peak value of 3.82 mT and decrease to 0 mT in 0.2 ms.

All participants will be asked to refrain from seeking any other physiotherapy or medications throughout the study period, especially during the first 5 weeks after enrollment, when PEMFs are proposed to be delivered. Whereas afterwards, during the follow-up phase when all participants are scheduled to receive only usual care, the use of analgesia and non-steroidal anti-inflammatory drugs (NSAIDs) will be permitted for the sake of ethical considerations. However, the use of this sort of medications should not exceed 3 days in each week and should not occur within 48 h of a follow-up visit. Information regarding the types of treatments and corresponding consumptions will be collected at each visit, and comparability between groups will be tested using Mann-Whitney’s *U*-test.

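### The per-protocol set for 6-month proximal femur BMD keeps participants who start non-permitted treatment after week 5, and on its natural reading does not depend on PEMF sessions received

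*Protocol article*

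**What the plan says.** In the protocol article, Data analysis makes intention-to-treat the primary approach and says that it keeps participants who are not fully compliant. It then adds: "we will conduct sensitivity analysis by conducting a per-protocol (PP) analysis for the primary outcome at 6 months". Membership of that set rests on two conditions: "It will include participants whose compliance is good, which is defined as attendance of all the scheduled visits, and low contamination", the latter spelled out as "no other treatment during the first 5 weeks after enrollment".

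Three other sections bear on these conditions.

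- **Interventions, exposure.** The course is "40 min/treatment, 1 treatment session/day, 6 treatment sessions/week, for a total of 30 times as one course of treatment". Sham participants receive sham treatment with the same device.
- **Interventions, other treatment.** "All participants will be asked to refrain from seeking any other physiotherapy or medications throughout the study period", with particular emphasis on the first 5 weeks. After that, "the use of analgesia and non-steroidal anti-inflammatory drugs (NSAIDs) will be permitted for the sake of ethical considerations", within limits on days per week and on timing before a visit. Types and amounts of other treatment are recorded at each visit and compared between groups with a Mann-Whitney test.
- **Follow-up.** The visits are "scheduled follow-up visits taking place at 5 weeks, 3 months and 6 months after enrollment".

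Assessment lists treatment compliance among the secondary outcomes, but Data analysis does not link it to the per-protocol set.

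**The concern.** A per-protocol analysis alongside intention-to-treat should show what happens among participants who were treated and followed as the protocol intended. Here the rule may not select them.

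On contamination, the filter stops at week 5 while the outcome is measured at 6 months. Treatment that affects bone and starts in between can move the outcome, yet it leaves the participant in the set. If it is more common in the sham arm it would tend to narrow the observed difference. If it is more common in the PEMF arm it would tend to widen it.

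On exposure, if attendance means the assessments, a participant who came to all three but to few treatment sessions counts as having good compliance. The analysis would then be close to an analysis of completers and would say little about whether poor adherence diluted the intention-to-treat estimate.

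The rule is stated in full in the article, so this is not a detail that an unshown analysis plan would be expected to supply.

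**Working it through.** **Step 1: planned exposure.** Interventions gives 6 sessions a week for 5 weeks: 6 × 5 = 30, which agrees with the stated total. At 40 minutes each, 30 × 40 / 60 = 20 hours.

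**Step 2: contamination window against restriction and endpoint.**

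| Item | Period | Section |
|---|---|---|
| Other treatment to be avoided | whole study period | Interventions |
| Analgesics and NSAIDs permitted, with limits | after week 5 | Interventions |
| Other treatment recorded | each visit | Interventions |
| Per-protocol contamination check | first 5 weeks | Data analysis |
| Endpoint of the per-protocol analysis | 6 months | Data analysis |

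Taking 6 months as 26 weeks, the check leaves out 26 − 5 = 21 weeks before the endpoint. The only relaxation in that interval concerns analgesics and NSAIDs. A participant who starts another bone-active treatment in week 6 departs from Interventions and still meets both per-protocol conditions. This does not depend on what visits means.

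**Step 3: what visits means.** Interventions calls the PEMF applications treatment sessions. Follow-up attaches the word scheduled to the assessments at 5 weeks, 3 months and 6 months, and Primary analysis also speaks of three follow-up visits. This favours the assessments. However, Data analysis omits the word follow-up and offers attendance as the definition of good compliance, so the sessions cannot be ruled out.

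- *Assessment reading:* no number of sessions is required, and anything from almost none to 30 is accepted.
- *Session reading:* 30 of 30 is required, and one absence excludes.

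**Step 4: how strict the session reading could be (illustration only).** The article gives no attendance rate. Assume every participant attends each session independently with the same probability p. The share attending all 30 is then p^30:

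| Assumed p | p^30 | Of 25 per arm | Of 20 per arm |
|---|---|---|---|
| 0.99 | 0.740 | 18.5 | 14.8 |
| 0.98 | 0.545 | 13.6 | 10.9 |
| 0.95 | 0.215 | 5.4 | 4.3 |

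The 25 and 20 per arm are the numbers in Sample size with and without the 20 % loss. If absences cluster in a few women, the share attending all 30 is higher at the same average attendance. The table shows that the two readings can give very different sets. It does not predict the size of either.

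**The case against.** The strongest reply is that the 5-week window has a visible reason. Interventions changes the rules at that point: abstinence is stressed for the treatment phase, and limited analgesic and NSAID use is allowed afterwards. Extending a condition of no other treatment unchanged to 6 months would exclude women for doing what the protocol allows. That stands, and it narrows the point to treatment that is not permitted. It does not explain why no treatment at all counts after week 5.

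A reader might infer that 21 of 26 weeks are unprotected. The document does not support that for the trial as a whole: the restriction runs throughout, and other treatment is recorded and compared between groups. Only the per-protocol filter stops at week 5. The between-group comparison, though, does not remove anyone from the set.

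A reader might also infer that the set certainly ignores the amount of PEMF received. That is the likelier reading but remains an inference, because on the session reading full attendance is required. What is certain is that the term allows two very different sets. Adherence will in any case be reported as a secondary outcome.

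Finally, requiring all assessments has merit: it gives a set without values carried forward for a missed assessment, a useful contrast with the LOCF-based primary analysis. Nothing here calls for that requirement to be dropped.

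**Conclusion.** The point holds in limited form and is minor. The contamination part is firm: Data analysis and Interventions do not agree for non-permitted treatment started after week 5, on either reading of visits. The exposure part is probable and rests on the article's use of words; at the least, the definition is ambiguous.

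No numerical effect on the 6-month estimate can be given, because the article states no adherence or contamination rates. A case such as bone-active treatment from week 6 is possible under the rule, but nothing in the article says how often it would occur.

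It would be wrong to conclude that the primary result is compromised. Primary inference is by intention-to-treat, per-protocol is a sensitivity analysis of one outcome, and Primary analysis plans a further sensitivity analysis by t-test. The sample size and the primary test do not depend on this definition.

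**What to change.** Reword the definition in Data analysis so that a participant is in the per-protocol set if all of these hold:

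1. She attended at least a stated share of the 30 sessions, active or sham, with the same threshold in both arms, fixed before unblinding.
2. She has a 6-month DXA.
3. She received no treatment outside what Interventions permits, from randomisation to the 6-month DXA. Usual care does not count as contamination, nor do analgesics and NSAIDs within the stated limits after week 5.

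If attendance at the assessments is kept as a further condition, name the three assessments so that the term cannot be read as the sessions. Interventions and Data analysis would then agree.

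The cost is small. Other treatment is already recorded at each visit and treatment compliance is already a listed outcome, although the article's text does not say when compliance is recorded. The set may become smaller or larger: removing late contamination shrinks it, and a minimum share admits more women than a demand for all 30 sessions would. Excluding participants for events after randomisation can introduce selection related to outcome, so the analysis should remain a sensitivity analysis beside intention-to-treat.
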